### Data collection

The participants will be asked to fill out three electronic questionnaires. At baseline, they will be asked to complete the demographic information form, Perceived Stress Scale (PSS), and Pittsburgh Sleep Quality Index (PSQI). After the completion of the intervention, they will be requested to complete the PSS and PSQI again (Fig. 1). Since the Iranian government has advised the public to minimize face-to-face interactions and isolate themselves at home during the COVID-19 pandemic, the electronic versions of the questionnaires will be used. Information on the app use, such as daily stress level and daily quality of sleep measured daily using the visual analog scale (VAS) in the web app, as well as the frequency of using different app sections will be collected, as well. Data on the app use and the possible use of other apps, including apps related to stress management, will also be collected.

### Outcomes

#### Primary outcome measure

The primary outcome of the study will be perceived stress, which will be assessed using the Perceived Stress Scale (PSS). PSS is a valid and reliable questionnaire used to measure stress among Iranian college students [43]. PSS contains 14 items scored based on a 5-point Likert scale ranging from 0 (never) to 4 (very often). Items 4, 7, 9, 10, and 13 are scored reversely. The total score of PSS will be obtained by adding all the items. The scores can range from 0 to 56, with higher scores representing the higher perceived stress.

#### Secondary outcome measure

The secondary outcome of the study will be sleep quality, which will be evaluated using the Pittsburgh Sleep Quality Index (PSQI). PSQI is a valid and reliable questionnaire used to measure stress among Iranian college students [44]. PSQI contains 18 items on a 4-point Likert scale ranging from 0 (not at all) to 3 (three or more times a week). These items index in seven subscales: subjective sleep efficiency, sleep latency, sleep duration, sleep quality, sleep disturbance, sleep medication use, and daytime dysfunction due to sleepiness. The total score ranges from 0 to 21 where higher scores indicate worse sleep quality. A PSQI score > 5 indicates poor sleep quality.

### Statistical analysis

The Kolmogorov-Smirnov test will be used to test the normal distribution of the data. The comparability of the intervention and control groups will be assessed at baseline. The quantitative variables will be described using mean and standard deviation if they follow a normal distribution and using median and range in case of non-normal distribution. The qualitative variables will be presented as percentages and confidence intervals. In order to compare the study groups regarding the mean scores of stress and sleep quality, the independent samples *t* test will be applied. In addition, the Mann-Whitney *U* and chi-square tests will be used to compare the two groups regarding non-parametric and categorical variables, respectively. In case of confounders, analysis of covariance or linear regression model will be used. Moreover, the paired samples *t* test will be utilized in order to compare the mean scores of stress and sleep quality in each group. Intention-to-treat analysis will be employed, as well. All analyses will be conducted using the SPSS 16 software, and *p* ≤ 0.05 will be considered statistically significant.

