### Sample size

The sample size is calculated based on a similar previous study [41] where the mean (SD) of perceived stress in groups 1 and 2 were 7.43 (2.93) and 9.49 (3.06), respectively. This study was a research aimed to evaluate the efficacy of a stress management app for college students. We chose this randomized controlled trial study because it was very similar to our study in terms of the intervention, outcome, and participants. After that, the sample size is calculated using the NCSS software. The minimum sample size based on power = 80%, and *α* = 0.05 is estimated at 35 individuals in each group. In order to compensate for the loss to follow-up, we will increase the sample size to 50 individuals in each group.

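### The analysis section leaves open whether a Kolmogorov-Smirnov result can turn the comparison of PSS and PSQI from means into ranks

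*Protocol article*

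**What the plan says.** All of the relevant text is in one paragraph of the protocol article, under Statistical analysis.

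- It opens with a normality test that names no variable: "The Kolmogorov-Smirnov test will be used to test the normal distribution of the data".
- Normality is tied explicitly to description only: "The quantitative variables will be described using mean and standard deviation if they follow a normal distribution". Otherwise the median and range are used.
- The test for both outcomes carries no condition: "In order to compare the study groups regarding the mean scores of stress and sleep quality, the independent samples *t* test will be applied".
- A rank test follows, with no variable named: "In addition, the Mann-Whitney *U* and chi-square tests will be used to compare the two groups regarding non-parametric and categorical variables".
- Adjustment is conditional: "In case of confounders, analysis of covariance or linear regression model will be used".

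Under Sample size, the trial is sized on a difference in means. The perceived stress values taken from the similar study "were 7.43 (2.93) and 9.49 (3.06), respectively".

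**The concern.** K-S is applied to the data without exception, and Mann-Whitney goes to variables called non-parametric. No variable is non-parametric in itself, and categorical variables go to chi-square. The phrase most naturally means quantitative variables that fail the normality test. PSS and PSQI are the two designated outcomes, and nothing says that their t test stands whatever K-S shows.

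If the switch were used, the hypothesis would change with the data: a difference in mean scores on one branch, an ordering of ranks on the other. The trial was sized on the first. If the switch were not used, a PSS that fails K-S would be summarised by median and range and tested on means, so the summary would not match the comparison. On either reading, the pre-test affects how the primary result is presented.

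**Working it through.** **1. Reproduce the sample size.** Inputs from the Sample size section: means 7.43 and 9.49, SDs 2.93 and 3.06, power 80%, alpha 0.05. Sidedness is not stated.

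- Difference: 9.49 − 7.43 = 2.06.
- Pooled SD: √[(2.93² + 3.06²)/2] = √[(8.5849 + 9.3636)/2] = 2.996.
- Standardised difference: 2.06/2.996 = 0.688.
- Normal approximation, two-sided: n = 2(1.96 + 0.842)²/0.688² = 33.2, so 34 per group.
- Exact two-sample t: 34.2, so 35 per group, the plan's figure. One-sided would give 27.
- Allowance for loss: 35/(1 − 0.30) = 50.

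The figure reproduces as a two-sided t test on means.

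**2. Does the choice of test change n?** The efficiency of Mann-Whitney relative to t under normality is 0.955, so 34.2/0.955 = 35.8, or 36 per group. Enrolling 50 covers this. Power of the t test is 0.81 at 35 and 0.93 at 50 per group. The sample size does not depend materially on the choice.

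**3. How often would K-S flag a sample?** The protocol gives no PSS distribution, so the shapes below are assumptions. Each entry is the share of single-arm samples flagged at 0.05 (2,000 simulations) at n = 35 / 50.

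| Assumed shape | K-S uncorrected | K-S with Lilliefors correction |
|---|---|---|
| Normal | 0.000 / 0.001 | 0.041 / 0.048 |
| Skewness 0.5 | 0.002 / 0.002 | 0.092 / 0.126 |
| Skewness 1 | 0.009 / 0.015 | 0.284 / 0.401 |
| Exponential (skewness 2) | 0.170 / 0.391 | 0.838 / 0.964 |

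A separate run of 4,000 simulations of the uncorrected test at skewness 1 gave 0.011 / 0.018. The uncorrected test thus flags about 1-2% of these samples and the corrected one 28-40%. The section names the software but not the version of the test, its level, or whether it is run pooled or by arm.

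**4. How often would the test switch, if a switch were applied?** Assume Mann-Whitney is used when either arm fails the Lilliefors version at 0.05 (4,000 simulations, n = 35 / 50).

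- Normal data: 0.097 / 0.097.
- Rounded PSS-like scores (assumed mean 28, SD 8): 0.146 / 0.176.
- Skewness 1: 0.481 / 0.641. As a check, 1 − (1 − 0.284)² = 0.487 and 1 − (1 − 0.401)² = 0.641.

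**5. Is the pre-test needed, and does it do harm under the null?** In the same runs, across the shapes simulated:

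- t test alone: type I error 0.045 to 0.057.
- Two-stage rule: 0.046 to 0.056.

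The Monte Carlo standard error is √(0.05 × 0.95/4000) = 0.0034, so both ranges lie within about two standard errors of 5%. The t test needs no protection from a normality gate at this size, and the gate does not materially inflate type I error.

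**The case against.** The strongest objection is that the gate is not written. The only sentence on stress and sleep assigns the t test outright, normality is linked in words only to description, and Mann-Whitney is introduced as an addition without naming PSS or PSQI. This stands in part. A reader might infer that K-S decides the primary test, but no sentence says so. The paragraph does not exclude the switch either, and the mismatch between summary and test remains if the t test is kept.

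Three further inferences are tempting, and the documents do not support them.

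- *K-S is uninformative at this sample size.* That holds only for the uncorrected version with mild to moderate skewness. With the Lilliefors correction, exponential data are flagged in 84-96% of samples. The protocol does not say which version is meant.
- *The error rate is inflated.* Taking the smaller p-value of t and Mann-Whitney gives 5.7-6.3% in simulation, and about 10-11% once change scores and ANCOVA are added. Those figures describe picking the best result, not a normality rule, and the section plans no between-arm comparison of change scores.
- *A switch to ranks loses the baseline adjustment.* The planned t test has none to lose, since ANCOVA or regression enters only if confounders are found.

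It can also be said that residual checks and sensitivity analyses belong in a fuller document that is not shown. That is fair for those details. The point here concerns a pre-test and a rank test that this text does state, and words ambiguously.

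**Conclusion.** The point holds as an ambiguity in the stated plan. The paragraph does not settle whether PSS and PSQI are compared by means or by ranks if K-S rejects normality, and it can pair a median summary with a test of means. If a switch is intended, an unstated version of K-S would strongly affect which hypothesis is tested: at skewness 1, about 1-2% against 28-40% of samples are flagged.

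The consequence is limited to an unfixed estimand and presentation of the primary result. The stated 35 per group reproduces and is unaffected. The frequencies rest on assumed distributions, 35 to 50 per arm, and a by-arm rule at 0.05. The ambiguity itself rests on the wording alone.

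**What to change.** State that PSS and PSQI are each compared between arms by one prespecified linear model (ANCOVA), adjusted for the baseline score and college and reported as a mean difference with confidence interval, whatever K-S shows. Both adjustment variables are already available: Data collection has PSS and PSQI completed at baseline, and Randomization uses a separate list for each college. This single model replaces the unadjusted t test, the possible switch to ranks and the ANCOVA that depends on finding confounders.

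Restrict K-S to descriptive use or delete it. Give the mean and SD of PSS and PSQI by arm in every case, with the median and range alongside if wanted. Keep Mann-Whitney for these two outcomes only as a labelled sensitivity analysis.

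The cost is wording: no new data and no change to 35 (50 enrolled) per arm. The one thing given up is a rank test as the primary analysis if scores prove heavily skewed, and it remains as a sensitivity analysis. Trial status reports that recruitment has closed, so the change should be dated and made before outcomes are compared by arm. Label: free improvement.

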### Procedures

All the participants will fill out the demographic data and other study questionnaires electronically. Then, the researcher will send a link to the intervention group to have access to the stress management app (Naranj) and another link to the control group to download an app unrelated to stress management.

The Naranj app includes a user profile, stress management strategies, consultation requests, and COVID-19 sections. The user profile includes account data, demographics, and health history (nutrition, physical activity, smoking, diseases, drug and alcohol consumption, etc.). Stress management strategies are based on the Acceptance and Commitment Therapy (ACT), Stress Reduction Theory (SRT), and some other evidence-based strategies. This section consists of various parts, including metaphors based on ACT, 4-7-8 breathing technique, Emotional Freedom Technique (EFT), pictures of nature, relaxing music, relaxing videos, educational quotes, my diary, forum, and meditation. In “my diary,” students have a space to enter their thoughts, emotions, and experiences of using the strategies. The “consultation request” section provides users with the opportunity to use emergency (receiving service during 24 h) and usual (receiving service during 48 h) consultations with psychological consultants. The “COVID-19” section provides educational content on COVID-19. In addition, this section is hyperlinked to the “stress management strategies” section. The Naranj app includes “privacy policy and terms of use,” app tutorial, contact us, and frequently asked questions, as well.

An app regarding calorie uptake management will be offered to the control group. This app is comparable to the Naranj app in terms of the need for daily use by the user. However, it is different from Naranj in terms of content. The rationale for using this app is to determine whether there will be an improvement in the outcome measures due to the stress management content in the Naranj app. Overall, both groups are provided with the same conditions. In this way, the effect of the confounding factors, if any, can be controlled and the Hawthorne effect will be minimized. According to the Hawthorne effect, individuals will alter their behaviors in response to being studied and usually refer to positive changes [42].

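### The between-group test of PSS and PSQI is unadjusted, with adjustment only if undefined confounders appear; pre-specified ANCOVA on the baseline score would add precision and settle the primary model at almost no cost

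*Protocol article*

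**What the plan says.** All references are to the protocol article.

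- **Primary outcome measure:** "The primary outcome of the study will be perceived stress, which will be assessed using the Perceived Stress Scale (PSS"). PSQI is the secondary outcome.
- **Procedures:** before any app link is sent, "All the participants will fill out the demographic data and other study questionnaires electronically".
- **Data collection:** "At baseline, they will be asked to complete the demographic information form, Perceived Stress Scale (PSS), and Pittsburgh Sleep Quality Index (PSQI"). Then: "After the completion of the intervention, they will be requested to complete the PSS and PSQI again". Each scale therefore has one baseline and one post-intervention value per participant.
- **Statistical analysis, between groups:** "In order to compare the study groups regarding the mean scores of stress and sleep quality, the independent samples" *t* test is named.
- **Statistical analysis, adjustment:** "In case of confounders, analysis of covariance or linear regression model will be used". The section does not say which variables could be confounders or how one would be recognised.
- **Statistical analysis, baseline:** "The comparability of the intervention and control groups will be assessed at baseline". The section does not link this check to the adjustment clause.
- **Randomization:** each college has its own permuted-block list, so allocation is stratified by college.
- **Sample size:** the two group means (SD) for "perceived stress in groups 1 and 2 were 7.43 (2.93) and 9.49 (3.06), respectively", giving 35 per group at 80% power and α = 0.05, raised to 50 for loss to follow-up.

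Apart from the baseline comparability check, the only analysis that clearly uses the baseline scores is the paired *t* test within each group, which does not compare the groups.

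**The concern.** In a randomised trial a baseline difference in PSS arises by chance. The reason to adjust for baseline PSS is that it is likely to predict follow-up PSS, and that reason holds whether or not an imbalance is seen. The plan makes adjustment conditional on confounders instead. After randomisation, a baseline variable could be called a confounder only by looking at the observed data.

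Two things are at stake:

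- **Precision.** The baseline score is collected from everyone, but the default test does not use it to reduce the residual variance.
- **Pre-specification.** With no covariate and no criterion stated, whether the primary result is the *t* test or an adjusted estimate, and adjusted for what, can be decided after the data are seen.

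**Working it through.** **Inputs from the Sample size section.** Means 7.43 and 9.49, SDs 2.93 and 3.06, α = 0.05, power 80%, 35 per group (50 after the allowance for loss). Sidedness is not stated.

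**Input not in the documents.** r, the correlation between baseline and post-intervention PSS. It is assumed to be 0.3, 0.5 or 0.7.

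**Step 1: reproduce the plan's figure.**
- Difference = 9.49 − 7.43 = 2.06.
- Pooled SD = √[(2.93² + 3.06²)/2] = 2.996.
- Standardised difference d = 2.06/2.996 = 0.688.
- Two-sided at α = 0.05, the normal approximation gives 34 per group.
- The noncentral *t* calculation gives power 79.8% at 34 and 80.9% at 35, so 35 per group. A one-sided normal calculation gives 27 and does not reproduce the figure.

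The stated 35 is therefore the size for an unadjusted two-sided *t* test. It takes no credit for baseline PSS.

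**Step 2: power with baseline PSS always in the model.** ANCOVA multiplies the residual variance by 1 − r², so the noncentrality is 2.06 / [2.996 × √(1 − r²) × √(2/n)]. With n = 35 and r = 0.5: residual SD = 2.996 × √0.75 = 2.594; noncentrality = 2.06/(2.594 × √(2/35)) = 3.32; power 91%.

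| Analysis | Residual variance relative to *t* test | Power, 35 per arm | Power, 50 per arm |
|---|---|---|---|
| *t* test | 100% | 81% | 93% |
| ANCOVA, r = 0.3 | 91% | 84% | 95% |
| ANCOVA, r = 0.5 | 75% | 91% | 98% |
| ANCOVA, r = 0.7 | 51% | 98% | over 99% |

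The ANCOVA rows allow one degree of freedom for baseline PSS. A second degree of freedom for college changes none of the rounded figures if college itself explains nothing.

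**Step 3: a conditional rule.** The plan's trigger is undefined, so one concrete version was simulated: the *t* test by default, and ANCOVA only if baseline PSS differs between groups at p < 0.05 (40,000 runs, 35 per arm).

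| r | Power, conditional rule | Power, always ANCOVA | Type I error, conditional rule |
|---|---|---|---|
| 0.3 | 81% | 84% | 4.7% |
| 0.5 | 82% | 90% | 4.3% |
| 0.7 | 83% | 97% | 3.6% |

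Under randomisation that trigger fires in only about 5% of trials, so the gain is almost entirely lost. The rule is slightly conservative. (The always-ANCOVA column is simulated and differs from Step 2 by about one point or less.)

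**Step 4: selection by result.** If both models were run and the smaller p value reported, the simulated type I error would be 6.3%, 7.3% and 8.2% at r = 0.3, 0.5 and 0.7. The plan states no such rule.

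**Step 5: if the *t* test is meant for change scores.** The text does not say whether post-intervention or change scores are compared. With equal SDs at both times, a change score has variance 2(1 − r) relative to the post-intervention score: 140%, 100% and 60% at r = 0.3, 0.5 and 0.7. ANCOVA has 91%, 75% and 51%, so it is the more precise analysis on either reading.

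**The case against.** The strongest reply is that nothing in the planned test is wrong. An unadjusted *t* test is unbiased after randomisation, holds its 5% error rate, and is the test for which the trial was sized. This stands. The plan delivers the power it promises, and the point is a missed gain, not an invalid result.

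Several further objections also stand, in whole or in part:

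- **Inflated false-positive rate.** A reader might infer from the open adjustment clause that the type I error is about 6–8%. The documents do not support that. It requires running both models and reporting the smaller p value, which the plan nowhere says. The conditional rule simulated above gives 3.6–4.7%. What can be said is that the undefined trigger leaves room for discretion.
- **Several competing p values.** A reader might count the *t* test, ANCOVA and linear regression as three. With the same covariates, ANCOVA and linear regression are one model and give the same treatment p value. The open choices are whether to adjust and for what.
- **Best-case sample size.** At 35 per arm the whole allowance for loss is used up, (50 − 35)/50 = 30%. With all 50 retained, the gain at r = 0.3 to 0.5 is 2 to 5 percentage points, against 3 to 10 at 35.
- **Baseline significance testing.** The plan says comparability will be assessed. It does not say that it will be tested, or that the result decides the covariates. The p < 0.05 trigger above is therefore only an illustration.

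One objection does not carry. A covariate list is commonly left to a statistical analysis plan, and its absence from a condensed article is no finding. Here, however, the article states both the unadjusted test and the conditional clause. The point concerns what is written.

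**Conclusion.** The point holds as a should-fix and a free improvement. The planned *t* test is valid and meets the stated 80% power. Two weaknesses remain: baseline scores collected from everyone do not sharpen the default between-group comparison, and the adjustment clause has no definition, so the primary model is not settled in advance.

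The precision loss depends on r, which the documents do not give. Over the assumed range of 0.3 to 0.7, the power forgone is about 3 to 17 percentage points at 35 per arm (81% against 84–98%) and about 2 to 7 at 50 per arm (93% against 95% to over 99%). These figures take the plan's standardised difference of 0.688 at face value and assume a two-sided 5% test, a linear relation between baseline and follow-up, and equal variances. The pre-specification weakness does not depend on r or on the number retained. It does not amount to a demonstrated inflation of the type I error.

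**What to change.** In the Statistical analysis section:

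1. Name one primary analysis: a linear model (ANCOVA) of post-intervention PSS on group, baseline PSS and college, fitted whatever the observed baseline balance. Report the adjusted mean difference with its 95% confidence interval. College belongs in the model because randomisation is stratified by it.
2. Use the same model for PSQI, with baseline PSQI in place of baseline PSS.
3. Remove the confounder trigger for the primary comparison, and state that the baseline comparison is descriptive and does not select covariates.
4. Keep the unadjusted *t* test as a supportive analysis, and say whether it compares post-intervention or change scores.

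The cost is wording and two degrees of freedom (baseline score and college). No new data and no change in sample size are needed. Recruitment is reported as closed, so the change should be dated and recorded before the outcome data are compared by group.

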### Design and setting

This is a non-blind, parallel-group (ratio 1:1), randomized controlled trial (superiority framework). The participants will be recruited from two colleges of Shiraz University of Medical Sciences in Iran: (1) School of Management and Medical Information (Health Information Management, Medical Informatics, and Health Services Management) and (2) School of Health.

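### Paired t tests within each arm are added at the same 0.05 level with no descriptive role, although they cannot answer the between-arm superiority question

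*Protocol article*

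**What the plan says.** The Statistical analysis section of the protocol article starts with the randomised comparison: "In order to compare the study groups regarding the mean scores of stress and sleep quality, the independent samples" t test is to be used, with Mann-Whitney U where a non-parametric test is needed. Adjustment is conditional: "In case of confounders, analysis of covariance or linear regression model will be used". The section then adds the paired samples t test, which "test will be utilized in order to compare the mean scores of stress and sleep quality in each group". One threshold covers every analysis: p "≤ 0.05 will be considered statistically significant".

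The section does not call the paired tests efficacy analyses, and it does not call them descriptive. Nor does it say that conclusions rest on the between-arm test alone.

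Elsewhere the trial is set up as a between-arm question. Design and setting states a parallel-group superiority framework. Sample size is built on a difference between two groups (means and SDs for "groups 1 and 2 were 7.43 (2.93) and 9.49 (3.06), respectively"). Procedures explains that the control app is there to isolate the effect of the stress-management content.

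**The concern.** Two arms times two outcomes gives four paired tests, on the primary outcome (PSS) and the only secondary outcome (PSQI). None of them uses the randomisation. Over three months of the outbreak, the change within one arm combines any app effect with several other sources:

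- the course of the epidemic;
- the academic calendar;
- the effect of being studied;
- regression to the mean, though entry does not require a high stress score.

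The active control removes these influences only when the arms are compared directly.

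The risk lies in how the results are read. If the app arm reaches p ≤ 0.05 and the control arm does not, the pair of results looks like evidence for the app. That contrast is not a test of the difference between arms, and it can appear when the difference is nil. The protocol has no rule for which result governs when the two kinds of test disagree.

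**Working it through.** **1. The plan's own figure.** Inputs from Sample size: means 7.43 and 9.49, SDs 2.93 and 3.06, power 80%, α = 0.05. Sidedness is not stated, so two-sided is assumed.

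- Difference: 9.49 − 7.43 = 2.06. Pooled SD: √[(2.93² + 3.06²)/2] = 2.996. Standardised difference: 2.06/2.996 = 0.69.
- n per arm = 2(1.960 + 0.842)² SD²/2.06². This gives 34 with SD 2.996 and 35 with SD 3.06. The t-based solution is 34.18, rounded up to 35.
- A one-sided calculation gives 26 to 28, which does not match.

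The stated 35 per arm is reproduced as a two-sided between-arm calculation. The trial is therefore sized for the between-arm test.

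**2. How often the misleading pattern arises with no treatment effect.** Assumptions not in the documents: both arms have the same true mean improvement c, the pre-post correlation is r = 0.5, and the data are normal.

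- SD of change = SD × √[2(1 − r)]. At r = 0.5 this equals SD, here 2.996.
- Non-centrality of each paired test = c√n / SD of change.
- u = chance of a significant improvement in one arm, and p = chance of significance in either direction, both from the noncentral t with n − 1 degrees of freedom.
- The arms are independent, so P(app arm significantly improved, control not significant) = u(1 − p).

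Example with no change: 0.025 × 0.95 = 0.024. Example with c = 1.0 and n = 35: u = 0.484, and 0.484 × 0.516 = 0.25.

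| Shared change (points) | In SD units | App only, n = 35 | App only, n = 50 |
|---|---|---|---|
| 0 | 0 | 2.4% | 2.4% |
| 0.5 | 0.17 | 13% | 17% |
| 0.75 | 0.25 | 21% | 24% |
| 1.0 | 0.33 | 25% | 23% |
| 1.25 | 0.42 | 22% | 15% |
| 1.5 | 0.50 | 15% | 6% |
| 2.06 | 0.69 | 2.3% | 0.3% |

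The ceiling is structural: p(1 − p) cannot exceed 0.25, and it reaches that value when each paired test has 50% power. Counting either direction (app only or control only), discordance peaks near 50%.

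**3. Sensitivity.** For r = 0.3 to 0.7 the peak stays near 25% and only its position moves. At n = 35 it lies near 1.25 points for r = 0.3 and near 0.75 points for r = 0.7. The result depends only on the standardised change, so it does not matter whether the planning SD suits the 0 to 56 scale of the PSS.

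**4. Comparison with the between-arm test.** In 100,000 simulated null trials (n = 35, r = 0.5), a between-arm t test on change scores rejected in 5.0% with no shared change and in 4.8% with a shared 1-point change. A two-sided 5% test falsely favours the app in 5%/2 = 2.5%. With the shared 1-point change, the app-only pattern appeared in 24.8% of trials, and in 91% of those the between-arm test was not significant.

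**The case against.** The strongest reply is that the protocol already asks and answers the right question. The between-arm test comes first, its purpose is stated, the trial is sized on it, and the design is a superiority trial. The paired tests are an addition and change neither the type I error nor the power of the randomised comparison. All of this stands, and it limits the severity.

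Three stronger readings are tempting, and the documents do not support them.

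- A reader might infer that the paired tests are planned as the analyses of effect, or that efficacy will be judged by contrasting their p-values. No section says so. The tests simply have no assigned role.
- A reader might infer that the protocol expects a Hawthorne effect in both arms, since Procedures says that "individuals will alter their behaviors in response to being studied and usually refer to positive changes". Those words define the effect. The same section says that giving both groups the same conditions will minimise it.
- A reader might infer that the misleading pattern is common whenever the app does nothing. It is common only if both arms share a moderate change. That is plausible in this setting, but the documents do not give it.

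It is also fair to say that the app-only rate is the rate of a pattern. It becomes a false claim only if the report sets aside the planned between-arm result.

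None of this shows that the paired tests inform the superiority question, or supplies the missing statement of their role.

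**Conclusion.** The point holds in a limited form. Four within-arm tests are planned at the same threshold as the randomised comparison, without a descriptive label, and they do not address the question the trial poses. With no treatment effect, the app-only pattern ranges per outcome from 0.3% to about 25% over the changes examined. Across 0.2 to 0.4 SD it is 17% to 25%, at either 35 or 50 per arm. The figures rest on an assumed equal change in both arms and, for the position of the peak, on the assumed correlation.

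Severity is minor to moderate. The valid test is in the plan and is unaffected. What is missing is a statement that it alone carries the conclusions.

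**What to change.** Remove the paired t tests as inferential analyses. Report the mean change in each arm with its 95% confidence interval, as description and without p-values. State that conclusions on stress and sleep quality rest only on the between-arm comparison at the end of the intervention, adjusted for the baseline score by analysis of covariance. Make that adjustment unconditional, not dependent on confounders being found.

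Cost: four within-arm p-values are lost. The analysis of covariance already named in the plan becomes the main between-arm analysis in place of the unadjusted t test, which is a real change to the plan and should be recorded as one. It needs no new data, because both scores are collected at baseline. Trial status reports that recruitment has ended, but only analysis and reporting are affected.
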